### Recruitment {15}

Study advertisements will be posted on local and digital media (e.g., Facebook, Instagram, Twitter). Participants will also be recruited from the UNC Hospital Carolina Data Warehouse for Health, which is a repository used for research participant recruitment in which patients of the UNC Health Care System can voluntarily enroll. Study flyers will also be posted at UNC clinical service units, including gynecology, primary care, psychiatry, psychology, and women’s health (Fig. 2).

**Fig. 2 Fig2:**
[figure not shown]
Schedule of enrollment, interventions, and assessments

## Assignment of interventions: allocation

### Sequence generation {16a}

Computer-generated randomization allocated participants to either active or placebo treatment condition without stratification.

### Concealment mechanism {16b}

After the determination of eligibility, the IDS will be notified to randomize the participant to either the estradiol (100 μg/day Climara® patch, or generic) or placebo (hydrocolloid patch) condition. Unblinded study medication will be dispensed to the study coordinator, who will blind and administer the medication to participants. In accordance with the study’s double-blind protocol, (1) all study personnel involved in the design, clinical outcome data collection, and analysis and (2) the research participant will be blind to treatment group assignment. The placebo and treatment patches will not contain any distinguishing information or feature visible to the research participant.

### Implementation {16c}

The study randomization list will be generated by an independent biostatistician and retained by the UNC Investigational Drug Service (IDS).

## Assignment of interventions: blinding

### Who will be blinded {17a}

For study personnel, the blind will be maintained by the UNC IDS until the end of the study, except for the study coordinator responsible for blinding and administering treatment.

### Procedure for unblinding if needed {17b}

Participants will be unblinded at the end of treatment/outcome data collection, at which point active treatment participants will commence 1 week of progesterone (200 mg/day, Prometrium® oral capsules, or its generic) combined with an additional week of estradiol (0.1mg/day, Climara® patch, or its generic) to stimulate menstruation and reduce the risk of endometrial hyperplasia.

## Data collection and management

### Plans for assessment and collection of outcomes {18a}

The primary clinical outcomes measures will examine anhedonia and psychosis-spectrum symptoms at treatment baseline, week one, week two, and the end of treatment (week 3). The Snaith–Hamilton Pleasure Scale (SHAPS) [38], a 14-item self-report questionnaire assessing hedonic behaviors with a score range of 14–56, will be used as a dimensional measure of anhedonia. The Brief Psychiatric Rating Scale, an 18-item, rater-administered scale measuring psychotic symptoms and anti-psychotic treatment response, will be used as a dimensional measure of psychosis [39, 40]. A psychosis subscale score will be calculated for primary analyses, consisting of scores from four items: conceptual disorganization, suspiciousness, hallucinations, and unusual thought content.

Additional measures will be collected to assess psychological and physiologic symptoms associated with the perimenopausal transition. Measures include the following:Inventory of Depression and Anxiety Symptoms (IDAS-II [56]), a 64-item self-report measure with good psychometric properties that has been validated for use with reproductive mood disorder samplesClinical Global Impression (CGI) scale [57]: assessment of functional impairment to be collected at pre-treatment, week one, week two, and post-treatmentLife Events Survey [58]: survey of stressful life events that may moderate effects of mood symptoms [59]Green Climacteric Scale [60]: 21-item gold-standard self-report measure for assessment of climacteric symptoms (vasomotor, somatic, anxiety, depression)Pittsburgh Sleep Quality Index (PSQI [61]): 9-item self-report questionnaire measuring sleep quality/patterns in older adultsDSM-5 Self-Rated Level 1 Cross-Cutting Symptom Measure—Adult [62]: self-report questionnaire assessing symptoms relevant across different mental health diagnosesThe 7-item anxiety scale (GAD-7) [63]: brief self-report anxiety scalePatient Health Questionnaire (PHQ)-9 [64]: brief 9-item questionnaire to assess depression severityWorld Health Organization Disability Assessment Schedule 2.0 [65]: self-report assessment of functioning across six domains (cognition, mobility, self-care, social interaction, life activities, participation)

These measures will be used in secondary and/or sensitivity analyses to examine the effect of covariates (in particular, climacteric symptoms, sleep quality, stressful life events).

### Plans to promote participant retention and complete follow-up {18b}

Participants will have the opportunity to receive up to $500 in total compensation for completion of study procedures. They will receive $60 for their first screening visit (completion of the SCID-5 and symptom questionnaires) and $30 for the second screening visit (blood panel and completion of a gynecological exam or medical records from an exam in the past three years). For the baseline and post-treatment PET-MR imaging sessions, participants can earn between $140 and $200 per session depending on their performance on the MID task. A variable compensation rate is necessary for these neuroimaging sessions to examine neural and molecular biomarkers related to motivation to win money. Furthermore, during weeks one and two of treatment, they will earn $55 per visit (brief interview, questionnaires to assess anhedonia/psychosis, and a blood draw). In the case of withdrawal from the study, a prorated payment schedule will be applied, including an hourly rate for PET-MR visits of $50 per hour and up to $150 total. Study coordinators are available to conduct clinical assessments at the home of participants or over zoom to increase retention and collect all clinical data.

### Compliance monitoring

Treatment compliance will be assessed via participant self-report. Blood samples will also be collected on a weekly basis as a biological measure of compliance. Samples will be used to measure serum estradiol levels using the enzyme-linked to immunosorbent assay (ELISA). In the event the study treatment protocol is not followed, the participant’s data will be excluded from analyses.

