#### Criteria for discontinuing or modifying the allocated intervention {11b}

Participants are free to withdraw from the study at any time, and this right will be reviewed during the consenting process. Investigators may discontinue study participation prior to completion of treatment for the following reasons: (1) intervention non-compliance; (2) the participant is lost-to-follow-up; (3) a medical condition or situation arises where continued participation is contraindicated; (4) a condition develops or an event occurs that meets exclusion criteria; (5) suicidal thoughts, plans, or intent is expressed; (6) or there are any other concerns about continued participation. In the case of severe mood symptoms or suicidal thoughts, the first three items on the Colombia-Suicide Severity Rating Scale will be administered by a member of the research team. If the participant expresses active suicidal ideation within the past week or expresses concerns about their ability to continue in the study, they will be evaluated by a licensed clinical psychologist or psychiatrist and will be discontinued from the study protocol. If symptoms are deemed otherwise unmanageable, inpatient admission to the university hospital’s psychiatry department will be arranged.

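### Serum estradiol can show a missed patch only in the estradiol arm, so excluding non-compliers on it can select differently by arm in the per-protocol primary comparison

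*Protocol article*

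**What the plan says.** The Compliance monitoring section of the protocol article names two measures. One is subjective: "Treatment compliance will be assessed via participant self-report". The other is biological: "Blood samples will also be collected on a weekly basis as a biological measure of compliance", and "Samples will be used to measure serum estradiol levels" by ELISA. The Intervention description places estradiol measurement at baseline, weeks one and two, and the end of treatment, which makes three on-treatment values per woman. The consequence for the data follows: "In the event the study treatment protocol is not followed, the participant’s data will be excluded from analyses". No threshold is given, and nothing says which of the two measures decides.

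The Statistical methods section {20a} analyses clinical outcomes both per-protocol and by intent-to-treat, but the mechanistic outcomes, which the Objectives call primary, per-protocol only.

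Four other sections bear on the point:
- Section {11b}: "Investigators may discontinue study participation prior to completion of treatment for the following reasons: (1) intervention non-compliance".
- Section {16b}: "all study personnel involved in the design, clinical outcome data collection, and analysis and (2) the research participant will be blind to treatment group assignment".
- Section {17a} keeps study personnel blind until the end of the study, "except for the study coordinator responsible for blinding and administering treatment".
- Section {19} has laboratory data entered and stored together with the clinical measures, with no mention of masking the estradiol values.

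**The concern.** Both arms wear a patch, but only one patch contains what the assay measures. Leaving off a placebo patch does not change serum estradiol, so the biological check is informative about missed patches in one arm only. If its result feeds the exclusion rule, hidden non-adherers leave the estradiol arm and stay in the placebo arm. Where non-adherers differ in outcome from adherers, the two arms are then no longer comparable. The primary mechanistic endpoints have no intent-to-treat analysis beside the per-protocol one to reveal this.

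The second issue follows from the first. A low value suggests non-adherence on estradiol and nothing on placebo, so whoever turns a value into a compliance decision needs the allocation. The article fixes the measure, the exclusion, the discontinuation ground and the list of blinded roles, but does not say how they fit together.

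**Working it through.** **The plan's own figure.** No stated number decides the point. The one figure that depends on how many estradiol women are kept is the smallest detectable correlation in that arm: r = .41 with n = 43 and 80% power (Sample size {14}). By Fisher z at two-sided 0.05:
- Detectable r = tanh((1.960 + 0.842)/√(43 − 3)) = tanh(0.443) = 0.416.
- Power at r = .41 = Φ(0.4356 × √40 − 1.960) = Φ(0.795) = 0.787. A noncentral t calculation gives 0.821.

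The stated figure therefore reproduces.

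**Inputs for the size of the effect.** The 85 analysable participants and the 43 in the estradiol group come from section {14}, which leaves 85 − 43 = 42 on placebo. Everything else is assumed:
- q: true non-adherence, equal in both arms.
- g: the outcome difference, in SD, between non-adherers and adherers.
- No true treatment effect.
- The assay catches every estradiol non-adherer.

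**Case A: no placebo non-adherer is removed.** The retained estradiol women have mean 0 and the placebo arm has mean q × g, so the bias is q × g in absolute size. Type I error comes from 20,000 simulated trials per row, using a two-sample t comparison of 43 against 42. That is a simplification of the planned mixed model, and its Monte Carlo standard error is √(0.05 × 0.95/20,000) ≈ 0.0015.

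| q | g (SD) | Bias (SD) | Type I error |
|---|---|---|---|
| 5% | 0.5 | 0.025 | 0.053 |
| 10% | 0.5 | 0.05 | 0.056 |
| 20% | 0.5 | 0.10 | 0.070 |
| 20% | 1.0 | 0.20 | 0.129 |

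For scale, the standard error of the difference between arms is √(1/43 + 1/42) = 0.217 SD. A bias of 0.05 SD is about a quarter of that (0.05/0.217 = 0.23), and 0.20 SD is nearly all of it (0.92).

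**Case B: half of the placebo non-adherers admit it and are also removed.** The non-adherent share left on placebo is (q/2)/(1 − q/2).
- q = 10%, g = 0.5: 0.05/0.95 × 0.5 = 0.026 SD.
- q = 20%, g = 1.0: 0.10/0.90 × 1.0 = 0.11 SD.

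Self-report at that level roughly halves the bias. In numbers of women, q = 10% removes 43 × 0.10 = 4.3 on estradiol against 42 × 0.05 = 2.1 on placebo. At q = 20% it is 8.6 against 4.2.

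**Cost to the estradiol-arm correlations.** Removing 5, 10 or 20% of 43 leaves 41, 39 or 34 women. Detectable r becomes .43, .44 or .47, and power at r = .41 becomes 77, 74 or 68%. This applies only if the 85 does not already allow for such exclusions; the Trial design section bases it on screen failures and dropout.

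**The case against.** The strongest reply has three parts.

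First, a reader might infer that the assay unblinds the investigators, or that the compliance rule contradicts the blinding section. The article does not support that. It never says when the ELISA is run, who receives the values, or that anyone acts on them during treatment; weekly collection is not weekly reporting. The non-compliance ground in {11b} is not tied to the assay and could rest on self-report or a detached patch. The study coordinator is outside the blind, and the Investigational Drug Service (IDS) holds the randomization list, so either could read the values without breaching {16b}. Routing of results is also something a journal article may leave to the full protocol. Nor is a single value a label of the arm: the Abstract and Background describe variable endogenous estradiol in these women, and no level or overlap between arms is given. This part of the reply stands, and only a risk remains.

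Second, a reader might infer that only women on estradiol can be found non-compliant. That is true of the assay for missed patches, but not of the whole check. Self-report applies to both arms, and an unexpectedly high value could flag a placebo woman taking estrogen from elsewhere. This also stands, and Case B shows what it is worth.

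Third, one-sided detection belongs to any drug-level assay against placebo, the effect at 5–10% non-adherence is small, and the clinical outcomes keep an intent-to-treat analysis. All true. But the article couples the assay to exclusion of data, and gives the primary endpoints no analysis free of that exclusion. That coupling is a choice the article makes, not a detail left to another document.

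**Conclusion.** The concern holds in limited form. As written, the compliance rule can remove women from the primary mechanistic comparison on evidence that exists for missed patches in one arm only, and that evidence cannot be interpreted without the allocation. The clinical outcomes are partly protected by their intent-to-treat analysis.

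The size is unknown and rests on assumed adherence. In the milder scenarios (5–10% non-adherence, 0.5 SD difference) the bias is at most 0.05 SD and type I error stays below 0.06. It becomes material (0.20 SD, about 0.13) only with 20% non-adherence, a full SD difference and no self-reported non-adherence on placebo. The direction depends on whether non-adherers do better or worse, which the article cannot tell us.

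Unblinding through the estradiol values is a risk that the article leaves open: investigators may act on non-compliance, and laboratory data are stored with the clinical measures. It is not shown to occur. The point should be addressed because the remedy is cheap and affects the primary endpoints, but it does not undermine the design.

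**What to change.** 1. In Compliance monitoring and Statistical methods {20a}, define compliance for the analysis sets by a criterion applied identically in both arms: self-report and the weekly patch-placement record.
2. State that no woman is excluded from a between-arm analysis on serum estradiol. Use the values as a descriptive measure of exposure, or in analyses confined to the estradiol arm.
3. State that estradiol results stay with the IDS or another unblinded person who has no outcome-assessment role, or that samples are assayed in batch, and that outcome staff and analysts do not receive them before database lock. The restriction on role matters because section {18b} has study coordinators conducting clinical assessments; whether one of them is the unblinded coordinator is not stated.
4. Reconcile the non-compliance ground in {11b} with the blinding described in {16b} and {17a}, so that it is clear what information the deciding person holds. What that ground should be is for the trial team.

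The cost is wording and laboratory flow. The coordinator already places patches weekly in both arms and participants already report loosening patches, so the patch record adds little work. The downside is small: some hidden non-adherence on estradiol stays in the between-arm comparison and is seen only after lock.

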#### Relevant concomitant care permitted or prohibited during the trial {11d}

To be eligible to complete the study, participants must not be taking any psychotropic medication or supplement that is known to alter the mood. Study participants who elect to begin taking such medications or supplements during the 3-week treatment window will be discontinued from the study.

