## Statistical methods

### Statistical methods for primary and secondary outcomes {20a}

The first objective of this study is to examine baseline (i.e., pre-treatment) associations between anhedonia and psychosis and neural and molecular responses to rewards. Associations between clinical measures and mechanistic outcomes will be estimated via correlation analysis. The second objective is to evaluate the experimental effects of estradiol versus placebo on clinical outcome measures and mechanistic outcomes. Mixed effects models will be used to examine the effects of time, treatment group, and their interaction on clinical outcomes (four timepoints, random intercept and slope) and neural and molecular outcomes (two timepoints, random intercept only), with age as a covariate. A separate model will be generated for each clinical outcome measure (anhedonia and psychosis) and each neural and molecular outcome (activation during reward anticipation and BP_ND_ and task-related ΔBP_ND_ for striatal regions of interest). Exploratory whole-brain analyses will also be conducted for fMRI activation during reward anticipation. Within the estradiol treatment group only, we will examine how biomarkers of reward response predict changes in clinical outcome measures. We will examine intercorrelations between anhedonia or psychosis and neural and molecular reward response, using residualized gain scores to quantify changes in clinical measures. We will also use mixed effect models to examine how changes in neural and molecular reward response predict variability in clinical outcome trajectories, with a separate model for each clinical outcome and each neural and molecular change score. Maximum likelihood estimation will be used in all mixed effect models to accommodate missing data (e.g., SAS proc mixed). When multiple comparisons are conducted to test a hypothesis, appropriate correction will be applied to achieve a corrected *p*-value of 0.05. For clinical outcome hypotheses, both a per-protocol and an intent-to-treat analytic approach (e.g., utilizing all available data, even for participants who did not finish treatment to completion) will be used. For mechanistic hypotheses, a per-protocol approach will be used, including only participants who completed the baseline PET-MR scan, 3 weeks of estradiol treatment, and the post-treatment PET-MR scan.

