### Methods in analysis to handle protocol non-adherence and any statistical methods to handle missing data {20c}

We will report any differences in consent, withdrawal, and loss-to-follow-up by randomization arm. We do not have plans for imputation for missing data.

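### The compliance rule excludes non-adherent women from all analyses, contradicting the planned intent-to-treat analysis of SHAPS and BPRS

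*Protocol article*

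**What the plan says.** Two sections of the protocol article set rules for the data of a woman who does not take treatment as planned.

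- Compliance monitoring, after describing self-report and weekly serum estradiol as the checks, ends: "In the event the study treatment protocol is not followed, the participant’s data will be excluded from analyses". The sentence is not limited to an analysis set or to an outcome.
- Statistical methods for primary and secondary outcomes {20a} plans two analyses of the clinical outcomes, per-protocol and intent-to-treat. It describes the second as "utilizing all available data, even for participants who did not finish treatment to completion". For the mechanistic (PET-MR) hypotheses it plans a per-protocol analysis only.

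The section on non-adherence and missing data {20c} does not reconcile the two. It says "We will report any differences in consent, withdrawal, and loss-to-follow-up by randomization arm" and "We do not have plans for imputation for missing data", and mentions no exclusion.

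**The concern.** The two rules cannot both be followed for the same woman. If the compliance rule governs, women are removed from the intent-to-treat SHAPS and BPRS models because of something that happened after randomisation. That set would then no longer be the randomised groups. Estradiol women with little exposure would be missing from it, so its estimate would drift toward the effect under full adherence, which the per-protocol analysis already addresses.

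The second objective tests estradiol against placebo on these symptoms, and section {18a} treats them as the primary clinical measures. Two readings remain open, and the choice between them could be made after the data are seen.

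**Working it through.** **Step 1: the rules side by side.** Take a woman who attends all four weekly assessments but leaves her patch off for part of the three weeks.

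| Analysis | Compliance monitoring | Section {20a} | Conflict? |
|---|---|---|---|
| Clinical, per-protocol | data out | data out | no |
| Clinical, intent-to-treat | data out | data in | **yes** |
| Mechanistic, per-protocol | data out | data out | no |

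The conflict lies in one row only, the intent-to-treat analysis of SHAPS and BPRS. This step needs no arithmetic, and the finding rests on it.

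**Step 2: how large could the effect be?** The article states no figure to reproduce, so this is an illustration.

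Inputs:
- From Trial design {8}: 100 enrolled and at least 85 analysable, so at most 100 − 85 = 15 women are expected to be lost for all reasons. This caps the assumed non-adherence at 15%.
- Assumed: week-3 SHAPS benefit B = 3 points with full adherence; a fraction q of each arm non-adherent (5%, 10% or 15%); non-adherent estradiol women keep a share f of the benefit (0 or 0.5); non-adherent women otherwise follow the same course as the rest.
- Assumed for precision: slope SD 1 per week, residual SD 3, 50 women per arm.

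With all data the expected benefit is B × [1 − q(1 − f)]. After exclusion it is B. The overstatement is therefore B × q × (1 − f):

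| q | f = 0.5 | f = 0 |
|---|---|---|
| 5% | 3 × 0.05 × 0.5 = 0.075 | 3 × 0.05 × 1 = 0.15 |
| 10% | 0.15 | 0.30 |
| 15% | 0.225 | 0.45 |

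A simulation agrees. It used 300,000 women per arm, visits at weeks 0 to 3, and a maximum likelihood mixed model with random intercept and slope (intercept SD 4.5, no age covariate). The estimate after exclusion was −2.99 throughout. With all data and f = 0.5 it was −2.92, −2.84 and −2.76 for q = 5%, 10% and 15%; with f = 0 it was −2.84, −2.69 and −2.54.

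**Step 3: compare with the precision.** Weeks 0, 1, 2 and 3 have squared deviations from 1.5 that sum to 2.25 + 0.25 + 0.25 + 2.25 = 5. The variance of one woman's slope is 1² + 3²/5 = 2.8. The standard error of the week-3 difference is 3 × √(2 × 2.8/n), with n women per arm:
- n = 50: 1.00
- n = 47.5 (5% excluded): 1.03
- n = 45 (10% excluded): 1.06
- n = 42.5 (15% excluded): 1.09

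The largest shift is 0.45/1.09 = 0.41 of a standard error.

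**The case against.** The strongest defence is that the compliance sentence is shorthand for the per-protocol set. The dedicated statistical section names both analysis sets, the section on non-adherence repeats no exclusion, and the rule fits the mechanistic analyses, which carry the primary endpoint. That may well be the intent. It does not cure the text, because the sentence says only that data leave the analyses, and an analyst reading it has no ground for narrowing it.

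The defence is right about size. According to Treatment arms, the coordinator places the patches weekly, with the same procedure for placebo, and treatment lasts three weeks. A non-adherence rate of 15%, which would use up the whole expected loss from all causes, is an extreme case.

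A reader might infer three stronger points that the article does not support.

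- *The intent-to-treat result would merely repeat the per-protocol one.* Section {11b} lists loss to follow-up and medical reasons separately from non-compliance, and also allows free withdrawal. Partial data from women who leave for those reasons would stay in the intent-to-treat set, so the two sets would still differ.
- *The exclusion would act differently by arm.* The article says "Blood samples will also be collected on a weekly basis as a biological measure of compliance", and serum estradiol says little about wear of a "placebo (hydrocolloid patch) condition". But staff place patches weekly in both arms, and {11c} provides blinded replacements for patches that start to come off, so detection on placebo does not rest on self-report alone. The article gives no serum threshold and describes estradiol as fluctuating in perimenopause, so full detection on estradiol would itself be an assumption. No arm difference can be quantified.
- *The stopping rules also contradict intent-to-treat.* For prohibited medication, {11d} reads "Study participants who elect to begin taking such medications or supplements during the 3-week treatment window will be discontinued from the study"; for suicidal ideation or concern about continuing, {11b} reads "they will be evaluated by a licensed clinical psychologist or psychiatrist and will be discontinued from the study protocol". Neither says whether symptom assessment goes on afterwards. A condensed article may leave that to the full protocol, and using scores up to the stop is consistent with analysing all available data. Any bias has no determinable sign, and collecting scores after a new drug starts is a choice of estimand.

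**Conclusion.** The contradiction is real. The compliance rule and the intent-to-treat clinical analysis give opposite instructions for non-adherent women, and no other section resolves them. It concerns SHAPS and BPRS only.

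The likely numerical consequence is modest: an overstatement of 0.075 to 0.45 SHAPS points, below half a standard error throughout. That range rests on the assumed benefit, SDs, non-adherence rates and retained benefit, with non-adherence equal in the two arms and unrelated to prognosis. The article supplies none of these, so the true size is unknown. If non-adherence is related to prognosis, the shift could differ from this range.

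The sponsor should correct the wording, because the status of the intent-to-treat result should not depend on which section the analyst follows.

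**What to change.** Reword the last sentence of Compliance monitoring so that the exclusion applies only to the per-protocol analyses, meaning the clinical per-protocol analysis and the mechanistic analyses. Add one sentence there or in {20a}: the intent-to-treat clinical models include all collected SHAPS and BPRS scores of every randomised woman, whatever her adherence.

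This needs no new data, visits or participants. It should be settled before the treatment groups are compared.

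As an optional addition, the sponsor could state whether women who stop the patch are invited to the remaining weekly assessments, using the home or video visits in {18b}. That would need an amendment and consent wording, and scores taken after a new drug starts would include its effect. The correction above does not depend on it.
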